# 1 INTRODUCTION

## 1.1 Background

Diminutive colorectal polyps ( $\leq 5$  mm) represent most of the polyps detected during colonoscopy, especially in the rectum-sigmoid tract. The characterization of these polyps by virtual chromoendoscopy is recognized as a key element for innovative imaging techniques. As a matter of facts diminutive colorectal polyps are very frequent and, if located in the rectosigmoid colon, they present a very low malignant risk (0.3% of evolution towards advanced adenoma and up to 0.08% of evolution towards invasive carcinoma). The real-time characterization would allow to identify the lowest risk polyps (hyperplastic subtype), to leave them in situ or, if resected, not to send them for histological examination, allowing a huge saving in healthcare associated costs.

Recently, the American Society for Gastrointestinal Endoscopy (ASGE) Technology Committee established the Preservation and Incorporation of Valuable endoscopic Innovations (PIVI) document, specific for real-time histological assessment for tiny colorectal polyps, to establish reference quality thresholds. Two performance standards have been developed to guide the use of advanced imaging:

1. for diminutive polyps to be resected and discarded without pathologic assessment, endoscopic technology (when used with high confidence) used to determine histology of polyps  $\leq 5$ mm in size, when combined with the histopathology assessment of polyps  $> 5$  mm in size, should provide a  $\geq 90\%$  agreement in assignment of post-polypectomy surveillance intervals when compared to decisions based on pathology assessment of all identified polyps;

2. in order for a technology to be used to guide the decision to leave suspected rectosigmoid hyperplastic polyps  $\leq 5$  mm in size in place (without resection), the technology should provide  $\geq 90\%$  negative predictive value (when used with high confidence) for adenomatous histology.

Computer-Aided-Diagnosis (CAD) is an artificial intelligence-based tool that would allow rapid and objective characterization of these lesions. The GI Genius CADx was developed to help endoscopists in their clinical practices for polyps characterization.

## 1.2 Software-aided colon polyp detection

GI Genius (also referred to as CB-17-08) CADe System is an Intelligent Endoscopy Module designed to be an adjunct to video colonoscopy with the purpose of supporting the operating physician with artificial intelligence during Colorectal Cancer Screening and Surveillance procedures.

To make GI Genius CADe System working, the module is placed on a shelf of a standard endoscopy tower and connected to both the video processor and the main display, both using the well-established SDI or HD-SDI video standards. The large part of the currently marketed endoscopy solutions is natively compatible with GI Genius CADe System, the few others can be connected using suitable adaptors.

As a result, the endoscopy video stream is flowing through the module with no modification or delay, without changing the way the endoscopy procedure is carried out.

At the same time, in real time, the module augments the video stream by adding small green overlay markers surrounding areas of interest, such that they can be further inspected and assessed independently according to the established standard clinical practice. Overlaid markers are further notified with a convenient sound.

GI Genius CADe System gives full control to the operating physician, being able to enable or disable the overlay markers at any time with a single touch.

**Figure 1.** GI Genius system on video endoscopy trolley.

[figure not shown]

[figure not shown]

### 1.3 Brief description of the investigational medical device

GI Genius CADx System is a software that, when installed in GI Genius CADe System (in the same hardware module of the CADe system), will add the ability to provide a histology prediction of framed polyps during real-time colonoscopy, with each polyp being classified as adenoma or non-adenoma. If the device is not able to reach a prediction, a no-prediction message will be displayed.

GI Genius CADx System (version 3.0.0) has received the CE mark as a class IIa medical device by an European Notified Body under the Medical Device Directive 93/42/EEC and subsequent amendments. GI Genius CADx System can therefore be legally marketed in Europe, and the study will be considered post-marketing.

## 2. STUDY RATIONALE AND DESIGN

### 2.1 Study objective

Primary object of the study is to prospectively evaluate if GI Genius CADx output can achieve  $\geq 90\%$  Negative Predictive Value in characterization (i.e. as adenomas or non-adenomas) of diminutive rectosigmoid polyps (i.e. PIVI 2), having conventional histopathology analysis of the resected specimens as reference standard. An exploratory objective of the study is to assess if there is an agreement between the post-polypectomy

surveillance intervals assigned by a combined use of GI Genius CADx as a means for optical diagnosis of diminutive ( $\leq 5$  mm) rectosigmoid polyps and conventional histology of polyps  $> 5$  mm, and those assigned by histology as unique means of diagnosis of all polyps (regardless of size or location).

## 2.2 Study rationale

The real-time characterization by GI Genius CADx would allow to identify the lowest risk polyps (hyperplastic subtype), to leave them *in situ* or, if resected, not to send them for histological examination, allowing a huge saving in healthcare associated costs. The study will assess prospectively if the use of GI Genius CADx provides a useful tool to perform real-time characterization of the colorectal polyps and if the device performances meet the PIVI guideline thresholds.

## 2.3 Risks and benefits of the investigational device and of the clinical study

### 2.3.1 Anticipated clinical benefits

The benefit for patients in participating in this study is that they will undergo with the most up-to-date GI Genius device, incorporating both detection (CADE) and characterization (CADx) features. There might also be a benefit for future patients, depending on the study results.

### 2.3.2 Risks associated with participation in the clinical study

No adjunctive risks are expected compared to standard endoscopic procedure. Endoscopy procedure will be performed according to the current best-practice.

## 2.4 Timeline

First patient is planned for enrollment on May 2021. The enrollment is expected to be completed in 4 months.

## 2.5 Sample size

A previous pilot study involving GI Genius CADx in 40 patients, reported an optical diagnosis of “non-adenoma” on 22 out of 23 assessed recto-sigmoid hyperplastic diminutive polyps, and could not reach an optical diagnosis on 1 polyp. The sample size calculation is therefore conservatively assuming that GI Genius CADx has an NPV between 95.6% (worst case analysis) and 100% on diminutive recto-sigmoid polyps and will therefore consider 97.8% as the expected NPV performance.

Using a one-sided alpha level of 0.025, a total of 148 subjects is required to achieve 80% power to meet the primary endpoint of the study. Anticipating a 5% drop-out rate, the target is to enroll at least 156 patients.

# **3 STUDY POPULATION**

## **3.1 Target population**

Patients aged 40 years or older undergoing colonoscopy for screening of colorectal cancer (CRC).

## **3.2 Inclusion Criteria**

- Patients aged 40 years or older undergoing screening colonoscopy for CRC;
- Ability to provide written, informed consent (approved by EC) and understand the responsibilities of trial participation.

## **3.3 Exclusion Criteria**

- subjects undergoing screening colonoscopy as part of the regional screening program for CRC;
- subjects undergoing CRC surveillance colonoscopy;
- subject at high risk for CRC;
- subjects with a personal history of CRC, IBD or hereditary polyposic or non-polyposic syndromes;
- patients with previous resection of the sigmoid rectum;
- patients on anticoagulant therapy, which precludes resection / removal operations due to histopathological findings;
- patients who perform an emergency colonoscopy.

# **7. STUDY VISITS AND PROCEDURES**

The following visits are foreseen for each subject:

## **1. Screening Visit**

A screening visit is performed at the investigational site. During this visit out-patients scheduled for colonoscopy will be informed about the background of the proposed study, the aims, procedures, inclusion and exclusion criteria, benefits and possible risks of the study prior to signing the informed consent form for inclusion in the study. If participating to the study is of interest to the subject, the informed consent form (ICF) will be discussed and presented. The subject must sign the ICF prior to enrolment. Possible clinical or laboratory examinations will be done, according to the local standard procedures. No procedures beyond the standard procedures in preparation to colonoscopy are foreseen per the current protocol. The date for the colonoscopy procedure to be performed at the investigational site will be scheduled. The screening visit can be performed on the same day of colonoscopy. The concomitant medications taken from the date of the informed consent up to the end of the colonoscopy visit will be recorded.

## **2. Colonoscopy visit**

Each eligible patient meeting inclusion/exclusion criteria who have agreed to participate to the study and have signed the ICF will undergo a colonoscopy examination performed by an experienced endoscopist. All polyps (mucosal lesions) detected during the colonoscopy will be removed with standard techniques of polyp resection. Bowel preparation, including split dose, will be done according to the standard protocols of the individual sites. The quality of bowel preparation will be assessed during colonoscopy using the Boston Bowel Preparation Scale (BBPS). Sedation according to the sites best experience and standard procedures will be delivered to the patient. Prior to undergoing colonoscopy, study subjects will undergo placement of intravenous catheter. Sedative medications (Midazolam, Meperidine, Propofol, etc.) will be administered as per local institutional practice if applicable. Women of child bearing potential will undergo a pregnancy test to exclude pregnancy prior to the colonoscopy if foreseen by standard procedures at the investigational site.

Study procedure:

Each patient will undergo standard white-light colonoscopy with the support of the latest version of CE marked GI Genius available.

Each polyp identified during the colonoscopy procedure will be first prepared for being characterized as follows:

white-light examination (use of virtual chromoendoscopy techniques [e.g. NBI, BLI, LCI] will not be allowed in this first step)

no zoom

washed properly

framed at 6 o'clock

framed at the nearest distance while keeping it on focus

framed steadily

The endoscopist will move around the target polyp until GI Genius CADx will provide an optical diagnosis.

The endoscopist will be asked to predict polyp's histology at this stage and will categorize it as either adenoma or non-adenoma along with the confidence of his assessment. This first prediction will be recorded in the study CRF.

Furthermore, the GI Genius CADx optical diagnosis will be recorded on the study CRF.

Subsequently, the endoscopist will switch on blue light virtual chromoendoscopy (i.e. NBI or BLI) and will be asked to record in the CRF his endoscopic assessment of the polyp: again, the endoscopist will predict polyp's histology at this stage and will categorize it as either adenoma or non-adenoma along with the confidence of his assessment. This second prediction will be recorded in the study CRF. Additionally, endoscopist will record polyp morphology (according to Paris classification), size and location (Cecum, Ascending colon, Transverse colon, Descending colon, Sigmoid colon and Rectum).

All the procedure will be video recorded from the beginning to the end with a recorder directly attached to the endoscopy video processor (prior to GI Genius), so to record the video without any additional overlay (i.e. without GI Genius CADe overlay).

All polyps will be removed, collected separately each from the other and stored in formaline at 10% to be analyzed by the local pathologists. All lesions will be classified by the pathologist according to the classification of Vienna. An advanced adenoma is defined as adenoma of 10 mm and/or with a villous component > 20% and/or high-grade dysplasia. Histology results will be recorded in the study CRF.

After the procedure has been carried out and data provided by the endoscopist has been properly recorded, before the availability of the histology results, without the presence of the patient and the endoscopist, the video recording will be reviewed by a team of endoscopists to get their optical biopsies and confidence about polyp adenomatous or non-adenomatous histology.

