## **15. Analysis plan:**

1. Test if the lower bound of the 95% CI of the GI Genius CADx optical diagnosis NPV for diminutive ( $\leq 5$  mm) rectosigmoid polyps is greater or equal than 90%.
2. Test if agreement in assignment of post-polypectomy surveillance intervals of the enrolled patients according to PIVI guidelines between:
  - a. the combined use of GI Genius CADx as optical diagnosis for diminutive ( $\leq 5$  mm) polyps and conventional histology as diagnostic tool for polyps  $> 5$  mm, and
  - b. histology as diagnostic tool for all the resected polyps (regardless of size).has a lower bound of the 95% CI greater or equal than 90%.
3. Report descriptive analysis of Sensitivity, Specificity, Accuracy, PPV and NPV of GI Genius CADx optical diagnosis
4. Report descriptive analysis of Sensitivity, Specificity, Accuracy, PPV and NPV of the optical diagnosis of endoscopists assessing lesions in white-light with the help of GI Genius CADx
5. Report descriptive analysis of Sensitivity, Specificity, Accuracy, PPV and NPV of the optical diagnosis of endoscopists assessing lesions with virtual chromoendoscopy and without the help of GI Genius CADx

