### 3. Endoscopic descriptions

For each polyp, the endoscopist will document if the polyp was characterized by the GI Genius CADx polyp characterization algorithm; additionally, the endoscopist will provide his own assessment of the predicted polyp histology, using the scale in Table 1 and Table 2.

**Table 1.** Endoscopist's assessment of the predicted polyp histology.

|                               |
|-------------------------------|
| Hyperplastic polyp (HP)       |
| Adenomatous polyp (AD)        |
| Sessile Serrated Lesion (SSL) |
| Cancer (CA)                   |
| Other non-adenomatous polyps  |
| Other/Undetermined (OU)       |

**Table 2.** Endoscopist's binary assessment of the predicted polyp histology.

|                   |
|-------------------|
| Adenoma (ADE)     |
| Non-adenoma (NOA) |

The endoscopist will also record the level of confidence of his assessment, which will be categorized as High or Low.

In addition, the endoscopist will record the location, the endoscopic appearance (morphology) and size of each colon lesion (polyp). Polyp morphology will be described based on Paris endoscopic classification of colon polyps (see **Table 3** and **Figure 2** below).

The colon lesions (polyps) are classified into 3 groups. Protruded lesions are classified Type I lesions, flat and elevated lesions as type II lesions and excavated lesions as type III lesions. Lesions classified as type lesions will be considered polypoid lesions; lesions classified as either type II or type III lesions will be considered non-polypoid lesions.

**Table 3.** Paris classification categories.

| Category     | Morphology | Description                    |
|--------------|------------|--------------------------------|
| Polypoid     | Ip         | Protruded, Pedunculated        |
|              | Is         | Protruded, Sessile             |
| Non-polypoid | IIa        | Superficial, elevated          |
|              | IIb        | Flat                           |
|              | IIc        | Superficial shallow, depressed |
|              | III        | Excavated                      |

**Figure 2.** Graphical representation of Paris classification categories.

[figure not shown]

The size of each lesion will be estimated by the endoscopist and will be reported as diminutive (size 0-5 mm), small (size 6-9 mm) or large (size 10 mm or larger).

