## 10 STUDY ENDPOINTS

### 10.1 Primary endpoint:

- Negative Predictive Value (NPV) of GI Genius CADx optical diagnosis on diminutive ( $\leq 5$  mm) rectosigmoid polyps.

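### In CHANGE, entry to the primary NPV set rests on the operator's own size and segment record, which nothing requires to be fixed before the CADx result is seen

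*Protocol*

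**What the plan says.** Section 10.1 of the CHANGE protocol sets the primary endpoint as "Negative Predictive Value (NPV) of GI Genius CADx optical diagnosis on diminutive" rectosigmoid polyps, with 5 mm as the upper size limit. The CHANGE synopsis, item 15, gives the criterion: "Test if the lower bound of the 95% CI of the GI Genius CADx optical diagnosis NPV for diminutive" rectosigmoid polyps is at least 90%.

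Two recorded facts decide whether a polyp belongs to that set, and the operator supplies both. Section 7, under Endoscopic descriptions, states: "The size of each lesion will be estimated by the endoscopist and will be reported as diminutive (size 0-5 mm), small (size 6-9 mm"; a third class covers everything from 10 mm upward. It also states: "In addition, the endoscopist will record the location, the endoscopic appearance (morphology) and size of each colon lesion (polyp").

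Section 7, under Colonoscopy visit, lists the steps for each polyp in this order (synopsis item 11 repeats it):

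1. White light, polyp washed and framed. "The endoscopist will move around the target polyp until GI Genius CADx will provide an optical diagnosis".
2. The operator makes a first prediction, with confidence.
3. "Furthermore, the GI Genius CADx optical diagnosis will be recorded on the study CRF".
4. Blue light is switched on and the operator makes a second prediction, with confidence.
5. "Additionally, endoscopist will record polyp morphology (according to Paris classification), size and location".

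The procedure is recorded on video without overlay. The endoscopists who later review it are asked only for an optical diagnosis and their confidence, not for size or location.

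**The concern.** Membership of a diagnostic accuracy analysis set should not depend on the index test result. Here the person choosing between 0-5 mm and 6-9 mm has watched CADx give its label and, on the listed order, has also formed a blue-light opinion. If that knowledge shifts borderline size calls, polyps enter or leave the NPV denominator for reasons tied to the result under test.

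The route that would flatter the device is easy to describe. A polyp that CADx calls non-adenoma but that looks adenomatous in blue light is recorded as 6 mm and drops out. If it was a false negative, an error has left the calculation. The size field also decides which polyps are assigned by CADx and which by histology in the exploratory surveillance-interval endpoint. A later analysis plan cannot restore blindness at data capture.

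**Working it through.** **Inputs.** The success rule is a lower 95% limit for NPV of at least 90% (synopsis item 15). The one-sided alpha is 0.025 (section 2.5). The protocol does not state how many CADx-negative diminutive rectosigmoid polyps it expects, so I assume n = 148 for illustration.

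**The plan's own figure.** Section 2.5 needs 148 subjects and allows 5% dropout: 148/0.95 = 155.8, so 156, as stated. The 148 itself is not reproduced from 97.8% against 90%. The score formula [(1.96·√(0.90·0.10) + 0.842·√(0.978·0.022))/0.078]² gives 83.2, so 84. That 148 counts subjects, whereas NPV counts CADx non-adenoma calls, and no yield per subject is given. An unstated conversion may explain the gap. Nothing below depends on it.

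**Step 1: one polyp at the boundary.** For x correct out of n, the exact (Clopper-Pearson) lower limit is the 2.5% quantile of Beta(x, n − x + 1). Re-sizing a polyp from 5 to 6 mm removes it, so n falls by one.

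| Scenario | x/n | NPV | Lower limit | Result |
|---|---|---|---|---|
| 8 false negatives | 140/148 | 94.6% | 89.6% | fail |
| One of the 8 sized out | 140/147 | 95.2% | 90.4% | pass |
| 7 false negatives | 141/148 | 95.3% | 90.5% | pass |
| One more false negative sized in | 141/149 | 94.6% | 89.7% | fail |

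The last two rows show the opposite movement.

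**Step 2: selective loss of false negatives.** With n = 148, success needs at least 141 correct, because 140 fails and 141 passes. Suppose true NPV is 90% and a share q of false negatives is sized out. The NPV among polyps that remain is

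p(q) = 0.90 / [0.90 + 0.10·(1 − q)]

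and the chance of success is P(X ≥ 141) for X ~ Binomial(148, p(q)), with analysed calls held at 148.

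| q (assumed) | p(q) | Chance of success |
|---|---|---|
| 0 | 90.0% | 1.6% |
| 10% | 90.9% | 3.6% |
| 20% | 91.8% | 7.7% |
| 30% | 92.8% | 15.5% |

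The first row lies within the planned 2.5%; the other three exceed it. The protocol gives no information on q.

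**The case against.** **List order is not a timed step.** A reader might infer that the protocol obliges the operator to size the polyp after CADx. It does not. The procedure introduces size with an additive word, and Endoscopic descriptions repeats the item with no sequence. This stands. What remains is that the protocol leaves the moment open, lists it last, and nowhere requires it before CADx.

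**Inflation is not established.** A reader might conclude that NPV will be biased upward. The documents do not show this. The operator does not know histology when sizing. Sizing up worrying polyps also removes true negatives that were misjudged, and reassurance from a non-adenoma label could push sizes down and bring false negatives in. This also stands: the direction is open and the shares in Step 2 are assumptions.

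**The example sits on the edge.** Any threshold rule flips there. At the planned NPV of 97.8%, 8 or more false negatives in 148 would occur with probability of only about 1.7% (Binomial, error rate 0.022). Nor does one polyp always reverse the result: with 100 calls and 5 false negatives (95/100, lower limit 88.7%), removing one gives 95/99 and 89.98%, still a fail. So Step 1 shows sensitivity, not bias.

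**Location is less exposed.** Segment is an anatomical finding, and only the sigmoid/descending border is open to doubt. The weight of the point falls on size near 5/6 mm.

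**Early sizing has a cost.** Sizing before washing and close framing would add error at the very boundary that matters. The fix must respect that.

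**Conclusion.** The point holds as a correctable weakness in how the CHANGE primary set is formed. The text establishes that the operator estimates size and records segment, that the same operator sees the live CADx result, that these entries define the primary set, and that nothing fixes them earlier or checks them independently.

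The text does not establish that any bias will occur or which way it would run. The size is therefore conditional. With an assumed 148 CADx-negative polyps, a single re-sized false negative can turn a fail (89.6%) into a pass (90.4%). Selective loss of 10% to 30% of false negatives would raise the chance of wrongly passing at a true NPV of 90% from 1.6% to between 3.6% and 15.5%.

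A reader might extend this to the Standalone CADx study. That would be wrong: its primary endpoint compares accuracy over all valid lesions and has no size or location restriction.

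**What to change.** Amend the procedure in synopsis item 11 and in section 7, Colonoscopy visit:

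- Make size class (0-5, 6-9, 10 mm or more) and colon segment the first CRF entry for each polyp.
- Record and lock both in white light once the polyp is washed and framed. Do this before the CADx label is shown if the display can be turned off, and in any case before blue light. Section 1.2 describes single-touch control only for the CADe detection markers, so the sponsor must confirm whether it covers the CADx label.
- Define the primary set from the locked values. Log any later change, but do not use it for the primary endpoint.

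The cost is a reordered CRF and a short added step per polyp, with no extra patients or procedures. If the CADx label cannot be hidden, locking before blue light still removes the blue-light impression as an influence, but sizing would not be fully blind to CADx, and the report should say so.
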